# Improving Medicines use in People with Polypharmacy in Primary Care (IMPPP): Protocol for a multicentre cluster randomised trial comparing a complex intervention for medication optimization against usual care

**DOI:** 10.3310/nihropenres.13285.1

**Published:** 2022-11-08

**Keywords:** polypharmacy, clinical trial, medicines optimisation, general practice

## Abstract

**Introduction:**

Polypharmacy is increasingly common, and associated with undesirable consequences. Polypharmacy management necessitates balancing therapeutic benefits and risks, and varying clinical and patient priorities. Current guidance for managing polypharmacy is not supported by high quality evidence. The aim of the Improving Medicines use in People with Polypharmacy in Primary Care (IMPPP) trial is to evaluate the effectiveness of an intervention to optimise medication use for patients with polypharmacy in a general practice setting.

**Methods:**

This trial will use a multicentre, open-label, cluster-randomised controlled approach, with two parallel groups. Practices will be randomised to a complex intervention comprising structured medication review (including interprofessional GP/pharmacist treatment planning and patient-facing review) supported by performance feedback, financial incentivisation, clinician training and clinical informatics (intervention), or usual care (control). Patients with polypharmacy and triggering potentially inappropriate prescribing (PIP) indicators will be recruited in each practice using a computerised search of health records. 37 practices will recruit 50 patients, and review them over a 26-week intervention delivery period. The primary outcome is the mean number of PIP indicators triggered per patient at 26 weeks follow-up, determined objectively from coded GP electronic health records. Secondary outcomes will include patient reported outcome measures, and health and care service use. The main intention-to-treat analysis will use linear mixed effects regression to compare number of PIP indicators triggered at 26 weeks post-review between groups, adjusted for baseline (pre-randomisation) values. A nested process evaluation will explore implementation of the intervention in primary care.

**Ethics and dissemination:**

The protocol and associated study materials have been approved by the Wales REC 6, NHS Research Ethics Committee (REC reference 19/WA/0090), host institution and Health Research Authority. Research outputs will be published in peer-reviewed journals and relevant conferences, and additionally disseminated to patients and the public, clinicians, commissioners and policy makers.

**ISRCTN Registration:**

90146150 (28/03/2019)

## Introduction

Polypharmacy is broadly the prescribing of multiple medicines to one individual, and although there is no consensus on how many medicines define ‘multiple’, polypharmacy is increasingly common irrespective of how it is measured
^
1
^. An ageing population and increasing multimorbidity are key factors driving polypharmacy, compounded by single-condition clinical guidelines recommending more intensive treatment
^
2
^. Given that the majority of prescribing occurs in primary care, where people with long-term conditions are increasingly managed, polypharmacy presents a particular challenge to general practice.

The use of multiple medications is often considered undesirable by patients
^
3
^, and can have a number of adverse consequences, including poor medication adherence, adverse drug effects, and increased service use, as well as medication errors, and reduced quality of care
^
2,
4–
8
^. Importantly, there is a need to differentiate appropriate polypharmacy (where medication use is optimised) from problematic polypharmacy (where medications are used inappropriately or where the intended benefit is not realised)
^
9
^. Medication optimisation strategies for managing polypharmacy therefore need to balance expected benefits and risks with patient goals and priorities, and should ideally not only demonstrate reductions in potentially inappropriate prescribing but also benefits to patient outcomes.

Recent national guidance on optimising care for polypharmacy has been produced in the UK, but it is not supported by high quality evidence of intervention effectiveness and cost-effectiveness
^
10–
13
^. Furthermore, there has been significant recent investment in pharmacists working in UK general practice
^
14
^ to improve effective and safe use of medicines, but again evidence of how best this resource can be utilised in the context of polypharmacy is lacking. A Cochrane review in 2018 identified 32 studies designed to optimise polypharmacy in older patients
^
15
^. Most of these were multifaceted complex interventions delivered by pharmacists. However, studies were of limited quality and convincing evidence of clinically significant improvements were lacking. Other trials conducted in UK primary care, such as PINCER
^
16
^ and DQIP
^
17
^ have demonstrated that prescribing can be improved by review of patients who trigger one or more potentially inappropriate prescribing indicators. However, these interventions focussed on a limited number (<20) of indicators of limited complexity, and it is therefore not known whether the same approach can be applied to optimising polypharmacy.

There is thus a need for general practice-based interventions which can improve the quality and safety of medication use in people experiencing polypharmacy.

## Methods

### Aims

The aims of the IMPPP trial are to evaluate the clinical effectiveness and cost-effectiveness of an intervention to optimise medication use for patients with polypharmacy in a general practice setting, and to examine intervention implementation.

### Outcomes

The primary outcome of the trial is the mean number of potentially inappropriate prescribing (PIP) indicators triggered per patient at 26 weeks after a pre-medication review eligibility check. The list of potentially inappropriate prescribing indicators is provided in the published
*Extended data* (Appendix 1)
^
18
^.

*A priori* secondary outcomes for the trial will also be measured at 26 weeks follow-up, and include quality of life, health service utilisation, and patient medication and safety outcomes (see
Table 1 for details).

**Table 1. T1:** Baseline measures and trial outcomes.

Outcome/measure	Instrument	Data source
**Participant socio-demographics**		
Age, gender		GP records
Ethnicity	7-category, based on census classification	Questionnaire ^ a ^
Socioeconomic deprivation	Area-based (home postcode) using English Index of Multiple Deprivation	Questionnaire
Miscellaneous other	Specific questions on education level, employment status, home circumstances	Questionnaire
**Primary outcome**		
Potentially inappropriate prescribing	>100 prescribing indicators (see *Extended data*, Appendix 1 ^ 18 ^)	GP records
**Patient reported outcomes**		
Quality of life	12-Item Short Form Survey (SF-12) ^ 19 ^ Visual analogue scale	Questionnaire
Medication adherence (patient- reported)	MARS questionnaire ^ 20 ^ Single question 5-point Likert scale	Questionnaire
Medication adherence (prescription refills)	Medication possession ratio ^ 21 ^	GP records
Burden of treatment	Multimorbidity Treatment Burden Questionnaire ^ 22 ^	Questionnaire
Medication literacy	Specific questions relating to overall understanding of rationale for medicines, plus 14 key therapeutic areas	Questionnaire
**Patient experience of review** (intervention arm only)		
Satisfaction with care	5-point Likert scale	Post-review questionnaire
Confidence in clinician	5-point Likert scale	Post-review questionnaire
Empathy	Selected 4 questions from CARE Measure ^ 23 ^	Post-review questionnaire
Shared decision making	9-item Shared Decision Making questionnaire, SDM-Q9 ^ 24 ^ 5-point collaboRATE scale ^ 25 ^	Post-review questionnaire
**Health and care service utilisation**		
Unplanned hospital admissions	Count of unplanned acute hospital admissions over previous 6 months	HES
Other hospital use	Count of Accident and Emergency (A&E) and outpatient attendances over previous 6 months	HES
Primary care consultation rate	Count of specific consultation types	GP records, Questionnaire
Other service use	Specific questions on frequency and nature of contact with different services (social care, private care, other community care, etc)	Questionnaire
**Patient/medicines safety outcomes**		
Medication-related admissions	Count of medication-related admissions (derived from ICD10 codes T36-T50, X40-44, Y40-Y84 in primary diagnostic position) over previous 6 months	HES
All-cause mortality		GP records ^ b ^

*Post-review questionnaire delivered to intervention practices only after completion of patient-facing review. All other measures recorded pre-randomisation, immediately post-eligibility check, and at 26 weeks follow-up, with exception of a. recorded pre-randomisation only and b. recorded at 26 weeks follow-up only. HES, Hospital Episode Statistics (national administrative records)*

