### Sample size calculation

We consider an average reduction in number of potentially inappropriate prescribing indicators (primary outcome) of 0.5 per participant to be clinically meaningful. Based on data on the distribution of these indicators in pilot work, the standard deviation of the average (mean) indicator count is 2.0. Previous related studies conducted by our research group have also found an intraclass correlation coefficient (ICC) of between 0.0126 (EFIPPS
^
26
^) and 0.036 (DQIP
^
17
^). Therefore, to detect a mean decrease in number of indicators triggered per participant of 0.5 in 50 participants per practice, with a power of 90% at the 5% significant level, and assuming an ICC of 0.036, we require a total of 37 practices. Due to the automated manner in which primary outcome data are captured, we expect approximately 100% follow-up; as the follow-up period is only 6 months, we expect few participants to withdraw, move away or die during this time. Even if 20% of cases are lost to follow-up, power will still be 88% at the 5% significance level with the same number of practices. Participant engagement with the medication review process in the pilot study was ≥88%.

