### Safety reporting

Given the nature of participants in the IMPPP trial (older individuals with polypharmacy and therefore likely with multimorbidity), new diagnoses, hospital admissions and death are to be anticipated. An independent Data Monitoring Committee (DMC) will be established to assess trial safety and efficacy, consisting of three independent academic members including two statisticians and a clinician with relevant interests. Serious adverse events will be monitored, recorded and reported in accordance with the Good Clinical Practice (GCP) guidelines and the Sponsor’s Research Related Adverse Event Reporting Policy. Adverse events may be reported by participant or investigator, and assessment of intensity, relatedness and expectedness will be made by the Principal Investigator at each research site for all serious adverse events. Suspected unexpected serious adverse reactions (SUSARs) will be reported to the coordinating centre within 24 hours, and discussed at each scheduled DMC meeting. SUSARs will be additionally reported to the trial Sponsor within 5 days and the Research Ethics Committee within 24 days. As there is a potential for
*ad hoc* adverse events to be more readily identified in the intervention arm, the Principal Investigator at all research sites (irrespective of randomisation status) will undertake an additional proactive review of all participants’ hospital admissions, GP consultations and deaths during the study period and at the end of study follow-up. This will help identify differences in adverse event rates between study arms.

An adverse event will be deemed to have occurred where a change to the prescribed medication is required to counter a change in medication made at the initial intervention (patient-facing review) appointment. An adverse event will be considered expected if a) an adverse drug reaction (ADR) has occurred (i.e. consistent with the WHO definition of ADR, listed in the British National Formulary (BNF)
^
27

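### As written, the HES count of medication-related admissions would rest largely on drug poisonings, because the primary-position rule is also applied to external-cause codes

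*Protocol article*

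**What the plan says.** The Outcomes section of the Protocol article says that the a priori secondary outcomes cover "quality of life, health service utilisation, and patient medication and safety outcomes". Under the patient and medicines safety heading of Table 1 there are two entries, all-cause mortality and medication-related admissions. The second is taken from HES and defined as "Count of medication-related admissions (derived from ICD10 codes T36-T50, X40-44, Y40-Y84 in primary diagnostic position) over previous 6 months". The qualifier on diagnostic position follows the whole list of codes. Nothing elsewhere in the article allows a secondary position or a separate cause field for any of the three ranges.

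By the Table 1 footnote, the measure is taken before randomisation, after the eligibility check and at 26 weeks. The Statistical analysis section adjusts each secondary outcome for its own baseline value.

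The Introduction lists "poor medication adherence, adverse drug effects, and increased service use" among the consequences of polypharmacy. The Safety reporting section treats drug reactions as a foreseeable harm of the intervention: "An adverse event will be considered expected if a) an adverse drug reaction (ADR) has occurred".

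**The concern.** ICD-10 uses two kinds of code here. T36-T50 describes a condition, namely poisoning by drugs. X40-X44 (accidental drug poisoning) and Y40-Y84 are external-cause codes: they say what brought a condition about and accompany the code for that condition. If a patient is admitted with a bleed or acute kidney injury from a medicine taken as prescribed, the primary diagnosis is normally the bleed or the kidney injury, and a Y40-Y59 code is added behind it. Under the Table 1 rule such an admission would not normally count.

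This is the only outcome in Table 1 that is specific to medication harm and compares the arms by one coded rule. If it consists largely of poisonings, similar counts in the two arms would say little about adverse drug reactions, yet they could be reported as no difference in medication-related admissions.

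**Working it through.** The article states no event rate, expected count or power for this outcome, so there is no figure to reproduce. The check is a reading of the definition against the structure of the classification it names.

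**Inputs.** From Table 1: the code ranges, the position rule and the data source. From general knowledge of how ICD-10 is built, not from the article: T36-T50 is poisoning, X and Y are external-cause codes, Y40-Y59 is drugs in therapeutic use, and Y60-Y84 is mainly misadventure, devices and procedures.

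**Step 1: what each range contributes under the rule as written.**

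| Range | Content | Normally in primary position? | Contribution as written |
|---|---|---|---|
| T36-T50 | Poisoning by drugs | Yes | Carries most of the count |
| X40-X44 | Accidental drug poisoning, external cause | No | Little; the poisoning itself is coded T36-T50 |
| Y40-Y59 | Drugs in therapeutic use, external cause | No | Little; most such reactions are missed |
| Y60-Y84 | Mainly misadventure, devices, procedures | No | Little; and mostly not medication |

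**Step 2: what the authors intended.** A definition meant for poisonings alone would not list Y40-Y59, the range for medicines in therapeutic use. Its inclusion shows that reactions to correctly used medicines were to be counted. The position rule works against that intention.

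**Step 3: how much is lost.** Let a be the share of true medication-related admissions that are therapeutic-use reactions, and q the fraction of those that do carry a Y40-Y59 code in first position. If every poisoning is coded T36-T50 in first position, then

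share captured = (1 − a) + a × q.

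On the usual convention q is small, so the share captured is close to 1 − a. Little is lost if a is near 0, and nearly everything if a is near 1. The article gives neither a nor q, so no figure can be put on the loss.

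**Step 4: the Y range.** Y40-Y84 spans 84 − 40 + 1 = 45 three-character slots. Y40-Y59 spans 59 − 40 + 1 = 20, and Y60-Y84 spans 84 − 60 + 1 = 25. So 25 of the 45 listed slots fall outside drugs in therapeutic use. These are counts of code labels, not of admissions. The excess has little effect while the position rule stands, but would admit procedural events if that rule were relaxed and the range left alone.

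**Step 5: reach of the problem.** The sample size is built on the prescribing indicator count, with a target difference of 0.5 and a standard deviation of 2.0. None of its inputs involves this outcome.

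**The case against.** Four counter-arguments deserve weight.

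- **The coding convention is not in the article.** This is true, and it limits the wording. A reader might infer that X and Y codes are never recorded first, so that the outcome counts only poisonings and will be near zero in both arms. The article has no event rates or code positions to support that. What stands is conditional on the ordinary use of external-cause codes: not normally first, and therefore largely poisonings.

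- **Harm is captured elsewhere.** A reader might infer that the trial has no means of detecting adverse drug reactions. The article does not support that. All unplanned admissions are counted from HES, so a bleed or a fall enters there, though without attribution to a medicine. Site Principal Investigators in both arms "will undertake an additional proactive review of all participants’ hospital admissions, GP consultations and deaths during the study period". This narrows the point but does not remove it. The Safety reporting section ties an adverse event to a medication change that counters one made at the intervention appointment, which control participants do not have, and relatedness is judged at site in an open-label trial.

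- **Primary position is a specificity choice.** It links the code to the reason for admission, which is reasonable for T36-T50. Applied to external-cause codes, it largely switches them off.

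- **Detail may sit in the statistical analysis plan.** That plan is not shown and might refine the algorithm. The point is not missing detail, however: Table 1 states both the codes and the position.

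Nor should Y60-Y84 be called wholly unrelated to medicines, since Y63 includes dosage failures. A claim that the review does not target overdose would also go beyond the article, because the indicator list and the full intervention description are in appendices that are not shown.

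**Conclusion.** The definition is at odds with its evident purpose. As worded, the HES count of medication-related admissions would rest largely on T36-T50 and miss most admissions for adverse reactions to correctly used medicines. The listed Y range also extends well beyond medication.

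The conclusion assumes that external-cause codes are used in the ordinary way in the HES data, and that the primary-position rule means what Table 1 says for all three ranges. The size of the loss is unknown.

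The consequence is limited to the validity of one secondary safety outcome. The point should be corrected before analysis. Until it is, a low or equal count is not evidence that medication harm is the same in both arms.

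**What to change.** Restate the outcome in Table 1 and carry it into the statistical analysis plan:

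- Apply the primary-position rule to T36-T50 only.
- Count X40-X44 and Y40-Y59 in any diagnostic or cause field of the admitting episode, with each admission counted once.
- Remove Y60-Y84, or keep only named subcodes that concern drug dosage and give the reason.
- Use the same definition at baseline and follow-up, since the baseline count is a covariate.
- Report poisonings and therapeutic-use reactions as separate components beside the total.

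If the authors meant the position rule for T36-T50 alone, saying so and naming the fields searched for the X and Y codes resolves most of the point.

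The cost is a change of wording and of the derivation code. No new data collection is needed, provided the HES extract includes the secondary diagnosis and cause fields; the article does not say, so this should be confirmed. The downside is that searching all positions will pick up some reactions that arose during the stay. Restricting the search to the first episode of the admission limits this but does not eliminate it.

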### Pilot study

A non-randomised pilot study, including three intervention practices and two control practices, has been completed to optimise intervention design and trial processes prior to the main trial. This provided provisional data on rates of potentially inappropriate prescribing and patient participant recruitment and retention. A formative process evaluation has also been carried out including interviews and observations with patients and practice staff. Findings from the pilot work have informed various aspects of the main trial protocol, and are summarised in the relevant sections below.

### Design

The trial will be a multicentre, open-label, cluster-randomised controlled trial, with two parallel groups (
Figure 1). Practices will be randomised to usual care (control), or a complex intervention comprising structured medication review involving both a pharmacist and a GP, supported by performance feedback, financial incentivisation, clinician training and clinical informatics (intervention). Patients with polypharmacy and potentially inappropriate prescribing will be recruited in each practice using a computerised search of health records. During the 26-week intervention delivery period, up to 50 patients in each intervention site will receive a medication review. Control practices will continue to provide usual care during this period. Every 4 weeks, over this 26-week period, a random sample of up to 10 consented patient participants in both intervention and control sites will be selected. An administrative eligibility check will be conducted to ensure the patient is still registered at the practice (if not, they will be excluded from the study). All eligible patient participants in intervention sites will then proceed to receive a medication review. Follow-up in both arms will then continue for 26 weeks after the eligibility check. Practices will continue to check eligibility for up to 10 patients every 4 weeks until they have confirmed a maximum of 50 eligible patient participants.

**Figure 1. f1:**
[figure not shown]
Trial flow diagram.

A cost-effectiveness analysis will be conducted. A parallel mixed-methods process evaluation will be undertaken to examine the implementation of the intervention to help explain its success or otherwise, and to inform subsequent implementation in clinical practice.

### Study setting

The trial will be undertaken in UK general practice, in two areas of England (Bristol and surrounding region, and the West Midlands).

### Trial participants

Eligible patient participants will be aged ≥18 years, willing and able to provide written informed consent, with 5 or more medicines listed on “repeat” irrespective of when last issued, and triggering at least one potentially inappropriate prescribing indicator (
*Extended data*, Appendix 1
^
18
^). Repeat medications are those recorded in the GP record as being currently available for repeated ordering by a patient without need for further consultation with a clinician; as such, they are generally accepted as representing long-term medication use.

Exclusion criteria will be screened for by a clinician (GP or pharmacist) in the practice, and are: 1) patients receiving end-of-life care; 2) patients judged by the clinician to have chaotic medication use (irrespective of cause); 3) patients for whom the clinician deems contact to be inappropriate (e.g. severe mental health problems, terminal illness, recent bereavement); 4) patients deemed by the clinician unable to complete the study questionnaires or medication review appointment (either themselves or with the help of carers); and 5) patients planning to move general practice within the 26-week follow-up period. We will report numbers of patients excluded in each group. A recent medication review outside the trial setting will not be considered an exclusion criterion, although it will be left to the clinician screening for inclusion in the study to decide if a second review in a short time as part of the study would be clinically appropriate.

